## Methods/design

### Aim and hypothesis

The primary aim of this trial is to investigate whether 6 weeks of binocular treatment leads to a greater improvement in amblyopic eye visual acuity than 6 weeks of a placebo treatment. The trial will also assess whether binocular treatment improves stereopsis and quality of life, and reduces interocular suppression to a greater extent than placebo treatment. Furthermore, compliance and participant acceptability of the home-based videogame treatment will also be addressed. We hypothesise that binocular treatment will lead to greater improvements in monocular (near and distance visual acuity) and binocular (stereopsis and suppression) visual function after 6 weeks of treatment compared to placebo treatment.

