#### Treatment allocation

Participants will be randomised to receive 6 weeks of active or placebo home-based binocular treatment in the form of an interactive falling-blocks game implemented on a 5th generation iPod touch device viewed through red/green anaglyphic glasses (Fig. 1). Participants will begin their treatment within 1 day of randomisation. Participants will be instructed to play the videogame for 1–2 h every day (separated into a maximum of three daily sessions) for 6 weeks while wearing red/green anaglyphic glasses and their optical correction where applicable. The treatment will terminate automatically on the iPod 44 days after randomisation, regardless of the scheduled follow-up clinical visit, to ensure consistent dosing for all participants. This trial uses a 6-week treatment period as previous studies indicate that this duration is sufficient for significant improvements [35, 37, 39, 40] and that compliance is high early in therapy but begins to fall after 6 weeks if the game is not changed.

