##### Control group

The placebo treatment game will be identical to the active treatment game except that both eyes will see the same images with no contrast offset. All participants will be required to wear red-green anaglyphic glasses on top of their optical correction during game play.

Both the treatment and placebo games include a dichoptically presented, contrast-balanced alignment calibration at the start of each treatment session. The participants will be presented with a dichoptic nonius cross that they are required to align using directional arrow buttons presented on the iPod screen. In the active game, the alignment information will be used to offset the relative position of the blocks shown to each eye to ensure proper alignment during game play.

The iPod devices will automatically record treatment information including contrast change, alignment calibration, scores achieved and compliance (time spent playing the game).

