#### Secondary outcomes

Change from baseline in best-corrected distance visual acuity in the amblyopic eye, fellow eye and both eyes at 3, 6, 12 and 24 weeks post randomisationChange from baseline in best-corrected near visual acuity in the amblyopic eye, fellow eye and both eyes at 3, 6, 12 and 24 weeks post randomisation measured using the Lighthouse ETDRS near visual acuity chartChange from baseline in stereopsis at 3, 6, 12 and 24 weeks post randomisation measured using Randot Preschool Stereotest [56]Change from baseline in angle of strabismus (where applicable) at 3, 6, 12 and 24 weeks post randomisation measured using the Simultaneous prism Cover Test at near and distance [22]Change from baseline in interocular suppression at 3, 6, 12 and 24 weeks post randomisation measured using Worth Four-dot Test at 33 cm and at 6 m and a prototype iPod-based version of the Dichoptic Motion Coherence Test [8, 10, 33]Change from baseline in interocular contrast at 3 and 6 weeks post randomisation based on the log file extracted from the iPodChange in quality of life from baseline to 24 weeks post randomisation measured in adult participants only (18 years of age or older) using the World Health Organisation Quality of Life (WHOQOL) – BREF [57]Treatment compliance at 3 and 6 weeks post randomisation. Participants’ compliance will be recorded in two ways: through data stored on the iPod device and through a diary provided to participants. Compliance will be defined as at least 25 % of the prescribed dose (i.e. playing the game for at least 5 h 15 min at 3 weeks and for at least 10 h 30 min at 6 weeks post randomisation) [37]Treatment acceptability at 3 and 6 weeks post randomisation, assessed using a modified version of the Amblyopia Treatment Index questionnaire for children and adults [58, 59]. This questionnaire has 5-point Likert Scales for a series of 20 questions for parents of participants aged 7–17 years and 19 questions for participants aged 18 years and overAdverse events. No cases of diplopia have been reported in published studies of contrast balanced binocular treatment, possibly because the treatment is designed to promote binocular function. However, diplopia is an important issue for any amblyopia treatment. Two cases of diplopia related to treatment using the I-BiT system have been reported and both cases resolved spontaneously following cessation of treatment [53]. Therefore, binocular treatment may carry a risk of diplopia. The potential side effect of diplopia will be monitored throughout the study. Diplopia will be discussed upon randomisation into the study and will be demonstrated using two sets of images, one printed on opaque paper and the other on a transparency. Participants and their caregivers (where relevant) will be asked to immediately report any experience of diplopia to their local study team. Study clinicians will also ask participants about diplopia at each follow-up visit and repeat the diplopia demonstration. If the participant reports diplopia at any time, the condition will be assessed by study clinicians using a diplopia questionnaire [60, 61] and standard clinical techniques will be used to assess the type of diplopia. If diplopia is confirmed, the study treatment will cease and the patient will be offered further treatment if required.

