#### Analyses

During the trial, data will be entered into a secure database with range checks for each data field. Anonymised paper copies of forms will be stored in secure locked filing cabinets. The final dataset will be made available to study team members upon approval from the Steering Committee.

The effect of the intervention will be evaluated between the active and placebo groups for the whole cohort and for each of three age groups; 7–12 years, 13–17 years and 18 years and over. This design will allow for a direct comparison to the current ‘gold standard’ clinical trial of monocular amblyopia treatment in older children (7–12 and 13–17 age groups) [22].

Statistical analyses will be performed using SAS version 9.4 (SAS Institute Inc. Cary, NC, USA) and will follow a prespecified statistical analysis plan. No interim analyses are planned. All statistical tests will be two-sided at the 5 % significance level. Treatment evaluations for the primary outcome will be carried out on an intention-to-treat (ITT) basis, where the ‘last value carried forward’ method will be used to replace missing data. Sensitivity analyses will be conducted to test the robustness of the primary outcome results. These will include per protocol analysis (excluding participants who have major protocol violations such as poor compliance, loss to follow-up and missing data), complete case analysis, and ITT analyses using multiple imputation to replace missing values in the primary outcome.

Baseline demographics, visual acuity, stereopsis, suppression, and quality of life will be summarised using descriptive statistics by treatment arms. The primary outcome and quality of life data will be analysed using linear regression. Repeated measures mixed models will be applied to other continuous outcomes measured repeatedly over time and the interaction effect between treatment and visit will be tested. For all continuous outcomes the baseline outcome value and age groups (stratification factor) will be adjusted for in the regression models. The model-adjusted treatment difference will be reported, with associated 95 % confidence interval and *p* value. Generalised linear regression models will be applied to categorical outcomes as appropriate. Results will be published and presented to the relevant professional groups.

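### Compliance is defined only as a yes/no cut at 25 % of dose although the device logs exact play time, so a material difference in exposure between the arms can go unseen

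*Protocol article*

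**What the plan says.** In the protocol article, Aim and hypothesis states that "compliance and participant acceptability of the home-based videogame treatment will also be addressed". Secondary outcomes lists compliance at 3 and 6 weeks, recorded by the device and by a diary, and then defines it: "Compliance will be defined as at least 25 % of the prescribed dose". In hours this is "at least 5 h 15 min at 3 weeks and for at least 10 h 30 min at 6 weeks post randomisation". A cited study is given as the basis for the threshold.

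Under Treatment allocation, participants are told to "play the videogame for 1–2 h every day" for six weeks. Under Control group, after both games have been described, the article says: "The iPod devices will automatically record treatment information including contrast change, alignment calibration, scores achieved and compliance (time spent playing the game".

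Analyses sends continuous outcomes measured repeatedly to mixed models and adds that "Generalised linear regression models will be applied to categorical outcomes as appropriate". It does not name compliance under either route. It refers to a prespecified statistical analysis plan, which is not at hand.

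**The concern.** This is a stated outcome definition, not a detail left open. It turns a continuous, automatically logged quantity into two classes, with the boundary low in the instructed range. Everyone from 10.5 h upwards falls into one class.

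The two arms play different games. In one, blocks are split between the eyes with a contrast offset that adapts to performance; in the other, both eyes see the same images. Engagement may differ for that reason alone. Whether exposure was comparable matters for reading either a positive or a null acuity result, and for judging home use. If most participants in both arms pass a low cut, the outcome as defined can show similar proportions while the hours differ substantially.

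**Working it through.** **The plan's own figures.** 25 % of 1 h a day gives 0.25 × 21 = 5.25 h at 3 weeks and 0.25 × 42 = 10.5 h at 6 weeks, which matches the stated cuts. The instruction of 1–2 h a day over 42 days spans 42–84 h. The top of that range is 84 / 10.5 = 8 times the cut, and both values score as compliant. Which reference dose the 25 % should refer to is a separate matter and is not raised here.

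**Inputs from the article.** There are 54 per arm with 10 % loss by 6 weeks (Sample size), so 54 × 0.9 = 48.6, taken as 49. On testing: "All statistical tests will be two-sided at the 5 % significance level".

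**Assumptions, because the article gives no figures for play time.** Play time is normal, possibly after transformation. The arms differ by a shift d of 0.5 or 0.6 SD. Between 50 % and 90 % of the better arm pass the cut.

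**Power on hours.** For a two-sample t-test with 96 degrees of freedom the non-centrality is d × √(49/2).
- d = 0.5: 2.475, power 69 %.
- d = 0.6: 2.970, power 84 %.

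**Power on the cut.** If a proportion p₁ of the better arm passes, the other arm passes with p₂ = Φ(Φ⁻¹(p₁) − d). With p̄ the mean of the two,

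power = Φ{ [(p₁ − p₂) − 1.96 √(2p̄(1 − p̄)/49)] / √([p₁(1 − p₁) + p₂(1 − p₂)]/49) }.

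Example with d = 0.5 and p₁ = 0.80: p₂ = 0.634, the difference is 0.166, and the two standard errors are 0.0910 and 0.0895. Power = Φ[(0.1663 − 0.1784)/0.0895] = Φ(−0.135) = 45 %.

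| Better arm passing | Cut, d = 0.5 | Cut, d = 0.6 |
|---|---|---|
| 50 % | 49 % | 63 % |
| 60 % | 50 % | 65 % |
| 70 % | 49 % | 64 % |
| 80 % | 45 % | 60 % |
| 90 % | 35 % | 49 % |
| Hours, for comparison | 69 % | 84 % |

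The loss is 69 − 50 = 19 to 69 − 35 = 34 points at d = 0.5, and 84 − 65 = 19 to 84 − 49 = 35 points at d = 0.6.

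**Skewed hours.** Assume log-normal play time with SD 0.8 on the log scale, a shift of 0.5 of that SD and 49 per arm. By simulation, an untransformed t-test has about 56 % power. Against the d = 0.5 column the loss is only 56 − 50 = 6 to 56 − 35 = 21 points. Analysing log hours restores the normal-shift result.

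**Early abandonment.** Assume 10 % of one arm and 30 % of the other stop below 10.5 h, and the rest play alike (mean about 35 h, SD 15 h), with 54 per arm. For the cut, p̄ = 0.80 and the standard errors are √(0.32/54) = 0.0770 and √(0.30/54) = 0.0745. Power = Φ[(0.20 − 1.96 × 0.0770)/0.0745] = Φ(0.66) = 75 %. A t-test on hours reaches about 43 % by simulation. Here the cut leads by about 32 points.

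**The case against.** Four points on the other side have weight.

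- **No planned test depends on it.** The hypotheses concern visual function and the sample size is built on acuity alone. Compliance has no stated effect size or power. This stands: no claim, alpha or sample size in the plan changes.
- **The definition does not forbid analysing hours.** Control group itself glosses the logged quantity as "compliance (time spent playing the game", and the unseen analysis plan may summarise or model it. A reader might infer that the article commits compliance to a generalised linear model and rules out hours. It does not: Analyses names no model for compliance and qualifies the categorical route with "as appropriate" wording. What remains is that the outcome, as defined in the article, is the cut and nothing else.
- **Power is an imperfect yardstick.** A non-significant test on hours would not show equal exposure either; an estimate with an interval is needed. This stands and shapes the fix.
- **The direction is not secure.** Dropping a home game early is a natural pattern, and in that case the cut is the more sensitive measure. This stands too, and is why the cut should be kept together with its comparison.

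The threshold also has a stated source and a plain use in saying who counts as compliant. The absence of a guideline behind it is no defect.

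**Conclusion.** The point holds as a minor one. The article defines compliance only by a low threshold while holding exact play time for both arms, so an exposure difference above the threshold would be invisible in the outcome as defined.

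The size is conditional: about 19–35 points of power under a normal shift of 0.5–0.6 SD, 49 per arm and 50–90 % of the better arm passing. It is less with skewed hours left untransformed, and of the opposite sign under early abandonment. A reader might take a fixed power loss to be a property of this trial. The documents do not support that, since they give no distribution, compliance rate or arm difference for play time. Nor do they support any inference that the primary result is at risk: the primary intention-to-treat analysis does not use compliance.

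**What to change.** In Secondary outcomes, add cumulative device-logged play time in hours at 3 and 6 weeks as a compliance measure next to the 25 % definition. Report the between-arm difference with a 95 % confidence interval at each visit, log-transformed or rank-based if the hours are skewed, adjusted for age group. Leave out the baseline covariate that Analyses prescribes for continuous outcomes, because Table 1 has no baseline compliance. Analysing the two visits separately avoids treating the 6-week total, which contains the 3-week total, as an independent repeat. Keep the 25 % proportion and its between-arm comparison alongside, since it is the better measure if the arms differ in early abandonment.

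The cost is a sentence or two of text and one extra secondary analysis. It needs no new data, visits or participants.

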
#### Sample size

Thirty-six participants (18 per arm) in each of the three age groups (7–12 years, 13–17 years and 18 years and over) will provide 90 % power at *p* = 0.05 to detect a group difference of 0.20 LogMAR [62, 63] in amblyopic eye distance visual acuity change at 6 weeks post randomisation between the two treatment arms, assuming a standard deviation of 0.17 LogMAR [32] and a 10 % loss-to-follow-up at 6 weeks. Each age group has been independently powered. Overall the study will aim to recruit a total of 108 participants (54 per arm) with 36 participants (18 per arm) in each of the three age groups (7–12 years, 13–17 years and 18 years and over).

#### Analyses

During the trial, data will be entered into a secure database with range checks for each data field. Anonymised paper copies of forms will be stored in secure locked filing cabinets. The final dataset will be made available to study team members upon approval from the Steering Committee.

The effect of the intervention will be evaluated between the active and placebo groups for the whole cohort and for each of three age groups; 7–12 years, 13–17 years and 18 years and over. This design will allow for a direct comparison to the current ‘gold standard’ clinical trial of monocular amblyopia treatment in older children (7–12 and 13–17 age groups) [22].

Statistical analyses will be performed using SAS version 9.4 (SAS Institute Inc. Cary, NC, USA) and will follow a prespecified statistical analysis plan. No interim analyses are planned. All statistical tests will be two-sided at the 5 % significance level. Treatment evaluations for the primary outcome will be carried out on an intention-to-treat (ITT) basis, where the ‘last value carried forward’ method will be used to replace missing data. Sensitivity analyses will be conducted to test the robustness of the primary outcome results. These will include per protocol analysis (excluding participants who have major protocol violations such as poor compliance, loss to follow-up and missing data), complete case analysis, and ITT analyses using multiple imputation to replace missing values in the primary outcome.

Baseline demographics, visual acuity, stereopsis, suppression, and quality of life will be summarised using descriptive statistics by treatment arms. The primary outcome and quality of life data will be analysed using linear regression. Repeated measures mixed models will be applied to other continuous outcomes measured repeatedly over time and the interaction effect between treatment and visit will be tested. For all continuous outcomes the baseline outcome value and age groups (stratification factor) will be adjusted for in the regression models. The model-adjusted treatment difference will be reported, with associated 95 % confidence interval and *p* value. Generalised linear regression models will be applied to categorical outcomes as appropriate. Results will be published and presented to the relevant professional groups.

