#### Outcomes

Outcome measures will be assessed at 3, 6, 12 and 24 weeks post randomisation by blinded assessors. Baseline and outcome measures are summarised in Table 1.

**Table 1 Tab1:** Schedule of assessments

	Randomisation	3 weeks	6 weeks	12 weeks	24 weeks
Demography	√				
Visual acuity	√	√	√	√	√
Stereopsis	√	√	√	√	√
Angle of strabismus (if applicable)	√	√	√	√	√
Interocular suppression	√	√	√	√	√
Interocular contrast		√	√		
Treatment compliance		√	√		
Treatment acceptability		√	√		
Quality of life (18 years and over)	√				√

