#### Primary outcome

The primary outcome is the change in best-corrected distance visual acuity in the amblyopic eye from baseline to 6 weeks post randomisation, measured using the highly standardised E-ETDRS protocol EVA testing system [55].

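### The primary 6-week analysis fills missing acuity by last value carried forward: a modest, avoidable bias in the headline estimate, although better methods are already in the plan

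*Protocol article*

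**What the plan says.** All places are in the protocol article.

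- Primary outcome: "The primary outcome is the change in best-corrected distance visual acuity in the amblyopic eye from baseline to 6 weeks post randomisation".
- Visits (Outcomes): "Outcome measures will be assessed at 3, 6, 12 and 24 weeks post randomisation by blinded assessors".
- Analyses, on the model: "The primary outcome and quality of life data will be analysed using linear regression", with adjustment for baseline value and age group.
- Analyses, on missing data in the primary intention-to-treat evaluation: "where the ‘last value carried forward’ method will be used to replace missing data".
- Analyses, on sensitivity: per-protocol, complete-case and "ITT analyses using multiple imputation to replace missing values in the primary outcome".
- Analyses, on further outcomes: "Repeated measures mixed models will be applied to other continuous outcomes measured repeatedly over time", with a test of the treatment-by-visit interaction.
- Secondary outcomes, first item: "Change from baseline in best-corrected distance visual acuity in the amblyopic eye, fellow eye and both eyes at 3, 6, 12 and 24 weeks".

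**The concern.** Only baseline and week 3 precede week 6, so only those two values can be carried forward. A participant with no 3-week visit is given a change of exactly zero. One with a 3-week visit is frozen halfway through a 6-week treatment. Either is correct only if acuity no longer changes after the last visit attended. The protocol expects otherwise: Treatment allocation justifies 6 weeks as long enough for improvement, and the Background cites an earlier trial in which every arm, control included, gained about 0.07 LogMAR.

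Three consequences follow. The estimated difference depends on how much is missing, when, and in which arm. The regression counts a filled-in value as a measurement. Someone who misses only week 6 but returns at weeks 12 and 24 contributes nothing from those visits. What is at stake is the trial's headline estimate, confidence interval and p value.

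**Working it through.** Improvement is counted as positive throughout.

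**Inputs from the protocol.** Difference 0.20 LogMAR, SD 0.17, 10 % loss at 6 weeks, 90 % power, 18 per arm per age group, 54 per arm overall (Sample size); two-sided 5 % (Analyses); control-arm gain 0.07 (Background, earlier dichoptic trial).

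**Assumptions not in the protocol.** The share *f* of the 6-week change already present in the carried value; any inequality of loss between arms; the within-person correlation; how many people who miss week 6 return later.

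**1. The plan's own figure.** n = 2(1.960 + 1.282)² × 0.17² / 0.20² = 15.2, so 16 per arm. 16 / 0.90 = 17.8, so 18 per arm, 36 per age group and 108 in total. This reproduces the protocol. Power with 16 completers per arm is 89.6 % (noncentral t).

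**2. Expected difference under carry-forward.** With 6-week gains g and loss proportions d in the active (A) and placebo (P) arms:

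E = g_A[1 − d_A(1 − f)] − g_P[1 − d_P(1 − f)]

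With equal loss d this is 0.20 × [1 − d(1 − f)]. At d = 0.10:
- baseline carried for all (f = 0): 0.20 × 0.90 = 0.180, 10 % low;
- 3-week value carried for all, half the gain present (f = 0.5): 0.20 × 0.95 = 0.190, 5 % low;
- half of those missing without a 3-week value (average f = 0.25): 0.20 × 0.925 = 0.185.

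**3. Power at 10 % loss.** Analytically, with 18 per arm and SD held at 0.17, power is 87.0 % for 0.180 and 90.3 % for 0.190, against 89.6 % planned. Simulation with the f = 0.25 mix gives 87–88 % for carry-forward against 89–90 % for complete cases, so about 2 points. For the whole cohort (54 per arm), power for 0.18 is above 99.9 %.

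**4. Unequal loss (hypothetical), true difference 0.20, gains 0.27 and 0.07, f = 0.25.**
- 15 % active/5 % placebo: 0.27 × 0.8875 − 0.07 × 0.9625 = 0.172. The range is 0.163 (f = 0) to 0.182 (f = 0.5).
- 5 % active/15 % placebo: 0.27 × 0.9625 − 0.07 × 0.8875 = 0.198, still slightly low.

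**5. No true effect (hypothetical), equal gain in both arms, f = 0.25, 54 per arm.** The spurious difference is gain × 0.75 × (d_P − d_A).

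| Gain | Loss placebo/active | Spurious difference | Simulated type I error |
|---|---|---|---|
| 0.07 | 15 %/5 % | 0.07 × 0.75 × 0.10 = 0.005 | 5.2–5.4 % |
| 0.07 | 25 %/5 % | 0.07 × 0.75 × 0.20 = 0.011 | 6.1–6.6 % |
| 0.10 | 25 %/5 % | 0.10 × 0.75 × 0.20 = 0.015 | 7.4–7.7 % |

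Ranges are across independent simulation runs. Reversing the arms reverses the sign.

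**6. Does the alternative do better?** Simulation with 54 per arm, 400 replicates, correlation 0.7, and half of those missing week 6 returning later. The repeated-measures model used all visits with unstructured covariance. Loss is active/placebo; true difference 0.20.

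| Loss, mechanism | Carry-forward | Complete case | Repeated measures |
|---|---|---|---|
| 10 %/10 %, completely at random | 0.187 | 0.202 | 0.202 |
| 15 %/5 %, completely at random | 0.172 | 0.198 | 0.199 |
| 10 %/10 %, dependent on week 3 | 0.190 | 0.200 | 0.200 |
| 15 %/5 %, dependent on week 3 | 0.177 | 0.212 | 0.200 |

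Complete-case analysis drifts when loss is unequal and depends on week-3 acuity. The repeated-measures model does not.

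**The case against.** The strongest reply is that little is lost. The only loss rate in the document is 10 %. At that rate the shift is 0.01–0.02 LogMAR against an SD of 0.17, it is towards the null, and the whole-cohort test is untouched. The larger figures need unequal loss that the protocol does not predict, and the highest type I error also needs a gain above the cited 0.07. All of that stands, and it limits the severity.

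The plan also names complete-case and multiple-imputation analyses as robustness checks, so a reader must not infer that missing data are otherwise unaddressed. A disagreement between methods would be visible. Even so, the headline result would still be the carry-forward one.

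Three stronger readings are tempting but unsupported:
- *Higher placebo loss makes the method favour active treatment.* Not in general. With a true difference of 0.20 and 5 % active/15 % placebo loss the estimate is about 0.198. A bias towards active treatment matters only when the true effect is near zero and loss is very unequal.
- *The plan already commits to a mixed model for this endpoint.* Analyses assigns linear regression to the primary outcome and mixed models to other continuous outcomes. That the mixed model covers amblyopic-eye distance acuity is inferred by reading this with the first secondary outcome. Multiple imputation, by contrast, is named outright for the primary outcome.
- *Leaving out weeks 12 and 24 is itself an error.* Those visits fall after play ends at day 44, so using them is a modelling choice. The defect is the substituted value and its treatment as observed.

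**Conclusion.** The concern holds at moderate size. Carry-forward is fixed as the primary method and, if acuity is still changing after the last visit attended, it biases the primary estimate. On the protocol's own figures the difference is attenuated by 5–10 %, to 0.18–0.19 LogMAR, with about 2 points of age-group power lost. That matters somewhat because Sample size states that each age group is powered independently. The whole-cohort test is barely affected.

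The 5–10 % range rests on between none and half of the 6-week gain being present in the carried value; if more is present, the bias is smaller. The unequal-loss results (about 0.17 at 15 % active/5 % placebo; 0.005–0.015 LogMAR and roughly 5 to 7.5 % type I error under the null) are illustrations, not predictions. They show that the direction depends on which arm loses more and on the true effect, so carry-forward cannot be defended as always conservative.

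**What to change.** Before unblinding, by documented amendment, replace carry-forward as the primary method with one of two options:

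1. The 6-week treatment contrast from a repeated-measures mixed model of amblyopic-eye distance acuity, with baseline acuity, age group, visit, treatment and treatment-by-visit terms (the simulation above used an unstructured covariance).
2. The multiple imputation already named for the primary outcome, promoted from sensitivity to primary.

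Keep carry-forward at most as a sensitivity analysis, and add a delta-adjusted analysis that shows how far the missing values would have to depart from the primary assumption to change the conclusion.

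No new data are needed and the sample size need not change. The cost is more than an edit to wording. Recruitment was scheduled to end on 31 May 2016 and the article cites a literature search of 25 September 2016, so the change comes late. It must be dated, justified and recorded while the team is still blinded.
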